#### Sample size calculation and statistical considerations

We hypothesize (null-hypothesis) that thermal ablation is non-inferior to surgical resection for the selected patient groups in terms of the primary objective (OS). The Cox proportional hazards model (1-sided; non-inferiority or superiority) is used for sample size calculations (Table 3). Given the superior safety profile we consider a hazard ratio (HR) of 1.3 to represent the upper limit of non-inferiority (non-inferiority margin). An HR of 1.3 corresponds to a 56.5% chance of the ablated patients to die first ((P = HR/(1 + HR) = 1.3/(1 + 1.3) = 0.565 (56.5%)). We will have reached 60% of events (death) approximately 6.5 years after having included the last patient (overall probability of event, pE = 0.6). The calculated sample size therefore is 599 (NS). To account for a 10% drop-out ratio (NDO = 69) prior to randomization and a 3% loss to follow-up (NLTFU = 18) after randomization we need to recruit 687 patients (NI). A total number of 618 patients (687–69 (NDO)) will be randomized (NR) into one of two arms: arm A will undergo surgical resection (*n* = 309) and arm B thermal ablation (n = 309) for appointed target lesions.

**Table 3 Tab3:** Sample size calculation

Significance level (α)	0.05
Power (1-β)	0.80
Hazard Ratio (HR), θ (non-inferiority margin)	1.3
Null-Hypothesis Hazard Ratio, θ_0_	1.0
Recruitment time/study accrual (months)	36
Follow-up time (months)	60
Ratio control vs. experimental: m_2_/m_1_	1.0
Total sample size (N_S_)/total number to be randomized (N_R_)	599
Accounting for 3% loss to follow-up after randomization (N_LTFU_)	18
Accounting for 10% drop-out ratio pre-randomization (N_DO_)	69
Initial pre-randomization sample size – number of included patients (N_I_)	687

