#### Primary and secondary objectives

The main objective is to prove non-inferiority of thermal ablation compared to hepatic resection in patients with at least one resectable and ablatable CRLM (≤3 cm) and no extrahepatic disease. Primary endpoint is OS. Main secondary endpoints are overall disease-free survival (DFS), time-to-progression (TTP), time-to-local-progression (TTLP), primary and assisted technique efficacy (PTE, ATE), procedural morbidity and mortality, length of hospital stay, assessment of pain and quality of life (QoL), cost-effectiveness ratio (ICER) and quality-adjusted life years (QALY).

Pain analysis will be performed using visual analogue scale questionnaires (VAS) assessed prior to, directly after and every 3 months after local treatment; administered pain medication will be registered. Quality of life analysis will be performed using European Organisation for Research and Treatment of Cancer Quality of Life questionnaires (EORTC-QLQ-CR29, EORCT QLQ-C30, EQ-5D) prior to, and every 3 months after local treatment. Patients who complete the quality-of life questionnaires at baseline and at least once during treatment and follow-up will be included in the analysis. The largest decrease in quality of life with respect to baseline will be calculated. The Wilcoxon rank sum test will be used to detect statistical differences between the two treatment arms.

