#### Statistical methods

All clinicopathological and procedural variables will be described and analysed. Continuous variables will be summarized with standard statistics including, means, standard deviations, medians and ranges. Categorical variables will be summarized with frequencies. When appropriate, box plots and cross tables will be used for descriptive statistics of continuous and categorical variables, respectively. *P*-values below 0.05 will be considered significant. All calculations will be generated by statistical package for social sciences software (SPSS®). Calculation of the number of patients that will be needed to address our primary endpoint with a power of 80% and a 5% type I error rate is described in the sample size calculation section.

Univariate survival analysis will be performed using the Kaplan-Meier method. Differences in survival lengths will be analysed using the log rank test. To determine hazard ratios (HR) for multivariate analysis, Cox regression will be used. Significance of differences for continuous and categorical data will be analysed using the Mann-Whitney U test and Chi-square test respectively. When appropriate, box plots and cross tables will be used for descriptive statistics of continuous and categorical variables, respectively. OS will be estimated by the Kaplan-Meier method with corresponding two sided 95% Cl’s for survival proportions.

Primary and assisted technique efficacy rates (PTE, ATE) defined as the percentage of target lesions that have recurred after the initial local treatment and after additional local treatments regardless of the technique(s) used to treat the recurrence with a minimum follow-up period of 12 months after the last focal therapy;- Direct and indirect total cost of care for both treatment arms will be registered in the cost-effectiveness data collection matrix. Based on this matrix a cost–utility analysis, measured in terms of years of full health lived, using quality-adjusted life years will be prospectively calculated. Cost-effectiveness will be expressed as an ICER, the ratio of change in costs to the change in effects.

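### Non-inferiority is stated as the null hypothesis, in the text and in Table 3, and the survival methods name only a test of difference, so the stated rules do not test the HR margin of 1.3

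*Protocol article*

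**What the plan says.** All places are in the protocol article.

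- **Primary and secondary objectives:** "The main objective is to prove non-inferiority of thermal ablation compared to hepatic resection", with overall survival (OS) as the primary endpoint.
- **Sample size calculation and statistical considerations, text:** "We hypothesize (null-hypothesis) that thermal ablation is non-inferior to surgical resection for the selected patient groups". The margin follows: "we consider a hazard ratio (HR) of 1.3 to represent the upper limit of non-inferiority (non-inferiority margin". The sizing is one-sided: "The Cox proportional hazards model (1-sided; non-inferiority or superiority) is used for sample size calculations".
- **Table 3:** the row "Null-Hypothesis Hazard Ratio" has the value 1.0. The row for the HR that is labelled as the margin has the value 1.3. Alpha is 0.05 and power 0.80.
- **Statistical methods:** "Differences in survival lengths will be analysed using the log rank test". P-values under 0.05 count as significant, with no sidedness given. Cox regression is assigned to HRs in multivariate analysis. The two-sided 95% intervals are for Kaplan-Meier survival proportions. The section gives 80% power and a 5% type I error for the primary endpoint and refers back to the sample size section.
- **Data monitoring:** the interim analysis of the primary endpoint is to be a non-inferiority analysis. No margin, level or confidence bound is given, and the final analysis is not mentioned there.

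**The concern.** In a non-inferiority trial the null is that the new treatment is worse by at least the margin, here HR ≥ 1.3. Non-inferiority is the claim that the data must establish by rejecting that null. The article has these roles the other way round in two places that agree with each other, so this is not a slip in a single word. The only survival test it then names, a log-rank test of difference, fits the reversed hypotheses and does not address the stated aim.

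The primary conclusion is at stake. Under the reversed null, a lack of evidence for a difference can be taken as support for non-inferiority, and a trial with fewer deaths finds that easier to achieve. Alpha and beta also change places: the 5% no longer limits the risk of accepting an inferior treatment, and the design's 20% type II error becomes that risk.

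**Working it through.** **Inputs.** Margin 1.3, one-sided alpha 0.05, power 0.80, 1:1 allocation, probability of death 0.6, 3% loss to follow-up and 10% drop-out before randomization (sample size section and Table 3).

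**1. Reproduce the plan's figure.** Deaths = 4(z₁₋α + z₁₋β)² / (ln 1.3)² = 4(1.645 + 0.842)² / 0.2624² = 359.3. Then 359.3 / 0.6 = 598.8, so 599. Also 599 / 0.97 = 618 and 618 / 0.90 = 687. All the planned numbers reproduce at one-sided 0.05. At one-sided 0.025 the formula gives 456.1 deaths and 456.1 / 0.6 = 760 patients, which does not match.

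**2. Why the reversal does not show in N.** The formula uses only the squared distance between the logs of the two HRs. Exchanging 1.0 and 1.3 leaves it at (ln 1.3)². N is therefore right for the intended test (null 1.3, assumed true HR 1.0), although the labels are wrong.

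**3. Error if the stated null is kept on a non-significant log-rank test.** With 359 deaths the standard error of the log HR is 2/√359 = 0.1056. At a true HR of 1.3 the expected z is 0.2624 / 0.1056 = 2.486.

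- One-sided 5% test: P(not significant) = Φ(1.645 − 2.486) = 0.20.
- Two-sided 5% test: P(not significant) = Φ(1.960 − 2.486) = 0.30 (the far tail is negligible).

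Both are to be compared with 0.05 for a proper test against the margin. The one-sided 0.20 is the design's own type II error. With 371 deaths (618 × 0.6 = 370.8) the values are 0.19 and 0.29.

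**4. The same contrast as observed HRs, at 359 deaths.**

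| Rule | Non-inferiority accepted if the observed HR is below |
|---|---|
| Upper one-sided 95% bound < 1.3 | 1.3 × exp(−1.645 × 0.1056) = 1.093 |
| One-sided log-rank not significant | exp(1.645 × 0.1056) = 1.190 |
| Two-sided log-rank not significant | exp(1.960 × 0.1056) = 1.230 |

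An observed HR between 1.093 and 1.190 (or 1.230) fails the margin test but would pass the other rule.

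**5. Direction when information is lower.** For illustration, assume 200 deaths. The expected z at HR 1.3 is 0.2624 / (2/√200) = 1.855, and the two-sided test is non-significant with probability Φ(1.960 − 1.855) = 0.54. The false acceptance rate rises as deaths fall.

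**The case against.** The best defence is that the intent is plain. The article says it wants to prove non-inferiority, fixes 1.3 as the upper limit, and sizes the trial with a one-sided Cox model, all of which point to comparing the HR with the margin. The log-rank sentence stands in a general account of univariate survival analysis and could equally serve disease-free survival and the progression endpoints. The full protocol or SAP, not shown here, may contain the decision rule. Correcting the labels leaves N unchanged.

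Much of this stands, and it limits the point in four ways.

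- **A reader might infer that the plan prescribes reading non-significance as non-inferiority.** No sentence says so. The reversed null permits that reading, so the 20% to 30% is conditional on it.
- **A reader might infer a conflict of levels, one-sided 5% for sizing against two-sided 95% for analysis, and hence that power is really 70%.** The documents do not support this. The two-sided 95% intervals are for survival proportions, not for the HR, and the 5% type I error in the methods refers back to the one-sided sizing.
- **A reader might infer that a non-inferiority analysis appears nowhere.** One is named for the interim, although without a margin or level.
- **The absence of a full decision rule is not in itself an error in a condensed article.**

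The defence does not remove what the article states wrongly: the null in the text, the null HR in Table 3, and a methods section whose only survival comparison tests for a difference. Clear intent makes the correction easy but does not replace it.

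**Conclusion.** The point holds in this form. The null hypothesis is reversed in the text and in Table 3, against the article's own objective, and the survival methods as stated do not test the 1.3 margin in the final analysis. If the stated null were kept on a non-significant log-rank result, the chance of accepting non-inferiority at a true HR of 1.3 would be about 20% (one-sided) to 30% (two-sided) instead of 5%. This assumes 359 deaths, proportional hazards and the usual normal approximation for the log HR. The range is needed because the article gives no sidedness for its p < 0.05 rule.

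The sample size is not in error: 599 is correct for a one-sided 5% test of the margin with a true HR of 1.0.

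**What to change.** 1. In the sample size section, state H0: HR (ablation/resection) ≥ 1.3 against H1: HR < 1.3.
2. In Table 3, give the null HR as 1.3 and the assumed true HR as 1.0.
3. In the statistical methods, state that the final OS analysis declares non-inferiority only if the upper one-sided 95% bound (the upper limit of the two-sided 90% CI) of the Cox treatment HR is below 1.3. This is the level that reproduces 599. Say also that a non-significant log-rank test is not evidence of non-inferiority.
4. If the full protocol or SAP already contains such a rule, align the wording with it.

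The cost is a few sentences and two table entries. Patients, deaths and follow-up do not change.

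One caution: if a two-sided 95% CI for the HR were chosen to decide, the observed HR would have to be below 1.3 × exp(−1.960 × 0.1056) = 1.057, and the stated power would have to be restated as about 70% at 359 deaths. The documents do not call for that choice.

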**Methods:**

In this two-arm, single-blind multi-center phase-III clinical trial, six hundred and eighteen patients with at least one CRLM (≤3 cm) will be included to undergo either surgical resection or thermal ablation of appointed target lesion(s) (≤3 cm). Primary endpoint is OS (overall survival, intention-to-treat analysis). Main secondary endpoints are overall disease-free survival (DFS), time to progression (TTP), time to local progression (TTLP), primary and assisted technique efficacy (PTE, ATE), procedural morbidity and mortality, length of hospital stay, assessment of pain and quality of life (QoL), cost-effectiveness ratio (ICER) and quality-adjusted life years (QALY).

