#### Inclusion

After having obtained written informed consent by the outpatient clinic doctor, patients will be formally included. The patient should be scheduled to undergo the procedure within a time-frame of maximum 6 weeks hereafter. Patients suitable for either laparoscopic resection or percutaneous ablation (Subgroup A, low disease burden; 1–3 target lesions) will be randomized prior to the procedure. All other patients will undergo open laparotomy with surgical inspection of the abdominal cavity and intra-operative ultrasound (IOUS).

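### Table 3 gives 599 as the number to be randomized, while the text beside it gives 618; 599 is the number needed after losses

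*Protocol article*

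**What the plan says.** The sample size section of the protocol article distinguishes three quantities in its text: a calculated sample size NS of 599, a number randomized NR, and a number recruited NI of 687. On NR the text is explicit: "A total number of 618 patients (687–69 (NDO)) will be randomized (NR) into one of two arms", with 309 in each arm.

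Table 3, in the same section, merges two of these. Its row "Total sample size (N_S_)/total number to be randomized (N_R" carries the single value 599. The next rows give 18 for a 3% loss after randomization, 69 for a 10% drop-out before randomization, and 687 for NI. No row shows 618. The Abbreviations list defines NS and NR as separate terms.

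The abstract uses a different verb for the 618: "six hundred and eighteen patients with at least one CRLM (≤3 cm) will be included". The Inclusion section places formal inclusion at consent ("After having obtained written informed consent by the outpatient clinic doctor, patients will be formally included"), and Table 3 applies the term included patients to the 687.

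**The concern.** One symbol, NR, has two values in one section, and it is the number to which the trial randomizes. The 599 label also conflicts with the table's own next row. If 599 is the number randomized, a loss that occurs after randomization comes out of those 599, and nothing has been added to cover it.

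A site, monitor or later author who takes the target from the table would randomize 19 fewer patients than the text intends. Two things depend on the target: the number of deaths expected at the planned event probability, and the points at which the Data monitoring section schedules its interim analyses (after 30% and 50% of patients have been randomized).

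**Working it through.** **Inputs, all from the protocol article**

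- One-sided test: "The Cox proportional hazards model (1-sided; non-inferiority or superiority) is used for sample size calculations" (sample size section).
- Significance level and power: "with a power of 80% and a 5% type I error rate" (Statistical methods; same values in Table 3).
- Margin: "we consider a hazard ratio (HR) of 1.3 to represent the upper limit of non-inferiority (non-inferiority margin"; the calculation takes the true hazard ratio as 1.0.
- Allocation 1:1 (Table 3).
- Overall event probability 0.6; 3% loss after randomization; 10% drop-out before randomization (sample size section).

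**Step 1: reproduce the plan's figures**

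Deaths required (Schoenfeld, 1:1):

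d = 4 × (1.645 + 0.842)² / (ln 1.3)² = 359.3

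- Patients needed after losses: 359.3 / 0.6 = 598.8, rounded up to **599** (NS).
- Patients to randomize: 599 / 0.97 = 617.5, rounded up to **618** (NR).
- Patients to recruit: 618 / 0.90 = 686.7, rounded up to **687** (NI).

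All three printed numbers reproduce. A two-sided 5% test would need 457 deaths, or about 762 patients, so the one-sided reading is the one behind the 599. The figure of 359 deaths is not printed; it is implied by 599 × 0.6 = 359.4.

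**Step 2: place 599 in the chain**

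The 599 comes before the division by 0.97, so it is the number that must remain once losses have occurred. The number to randomize is the next link, 618.

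**Step 3: what randomizing 599 would give**

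Power = Φ(ln 1.3 × √d / 2 − 1.645), assuming that patients lost to follow-up contribute no deaths:

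| Randomized | Retained (× 0.97) | Deaths (× 0.6) | Power |
|---|---|---|---|
| 618 (text) | 599.5 | 359.7 | 80.0% |
| 599 (Table 3 label) | 581.0 | 348.6 | 78.9% |

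Sensitivity to the assumption: if only about half of the 18 losses are removed, 599 − 9 = 590 patients give 354 deaths and 79.5%. If none are removed, 599 patients give 359.4 deaths and 80.0%.

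**Step 4: interim triggers**

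- NR = 599: 30% is 179.7 and 50% is 299.5, about 180 and 300 randomized.
- NR = 618: 30% is 185.4 and 50% is 309, about 185 and 309 randomized.

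**Step 5: do the table rows add up?**

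599 + 18 = 617 and 599 + 18 + 69 = 686, each one short of the printed 618 and 687. The 18 is 3% of 599 (17.97), whereas the text's figure comes from dividing by 0.97, which gives 618 − 599 = 19. With 19 the rows close: 599 + 19 + 69 = 687. This is one unit of rounding.

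**The case against.** The best defence is that the target is not really in doubt. The text states 618 with its subtraction and the per-arm numbers. Table 3 also leads back to it, because it adds the loss on top of 599 on the way to 687, and 687 − 69 = 618. On this view only a label is wrong and the allowance is still there. That stands as to intent, but the label still gives the wrong value for NR.

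The power figure can also be challenged. Deaths depend on follow-up as well as on enrolment. The Design section plans at least 10 years of follow-up, while the 60% event fraction is expected about 6.5 years after the last inclusion. With 581 patients retained, 359.3 deaths would need an event fraction of 359.3 / 581 = 61.8%, so somewhat longer follow-up could recover the shortfall. Patients lost late may also have died before loss and been counted. Both points stand: 78.9% applies at an event probability of 0.6 and is the pessimistic end of a range up to 80.0%.

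A reader might go further and infer that enrolment is stated in three incompatible ways, taking the abstract's 618 as patients counted at consent. That would leave 618 × 0.90 = 556 randomized, 539.5 retained, about 324 deaths and 76.3% power. The document does not support this. The abstract speaks of patients included to receive one of the two treatments, which most naturally means randomized. The Exclusion (drop-outs) section says that patients failing re-confirmation before randomization cannot be included, and the Randomization and Data monitoring sections use the same word for patients already in an arm. Read that way, the abstract agrees with the text and delivers the same deaths. What remains is a word used in two senses.

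**Conclusion.** There is one firm numerical contradiction: NR is 599 in Table 3 and 618 in the text. The plan's own chain settles it in favour of the text, because 599 is the number needed after the 3% loss.

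The consequence is small. If the table's label were followed, power would be 78.9% instead of 80.0%, with about 349 deaths instead of about 360. This rests on a one-sided 5% level, a true hazard ratio of 1.0, an event probability of 0.6, a full 3% loss, and no deaths counted among those lost. The interim looks would fall about 5 and 9 patients earlier.

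The trial as described in the text is not underpowered by its own assumptions. The abstract's verb is a wording point, and the one-unit gap in the table's sums is rounding; neither is a separate error.

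**What to change.** - **Table 3:** label 599 as NS only and add a row NR = 618 (309 per arm).
- **Loss allowance:** print 19 (618 − 599) in place of 18, in the table and in the text, so that 599 + 19 + 69 = 687.
- **Abstract:** say that 618 patients will be randomized, so that the figure does not clash with the 687 described elsewhere as included.

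This costs one relabelled row, one added row, one digit in two places and one verb. Intended enrolment, design and analysis do not change, and with NR fixed at 618 the interim triggers have a single denominator.

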#### Statistical methods

All clinicopathological and procedural variables will be described and analysed. Continuous variables will be summarized with standard statistics including, means, standard deviations, medians and ranges. Categorical variables will be summarized with frequencies. When appropriate, box plots and cross tables will be used for descriptive statistics of continuous and categorical variables, respectively. *P*-values below 0.05 will be considered significant. All calculations will be generated by statistical package for social sciences software (SPSS®). Calculation of the number of patients that will be needed to address our primary endpoint with a power of 80% and a 5% type I error rate is described in the sample size calculation section.

Univariate survival analysis will be performed using the Kaplan-Meier method. Differences in survival lengths will be analysed using the log rank test. To determine hazard ratios (HR) for multivariate analysis, Cox regression will be used. Significance of differences for continuous and categorical data will be analysed using the Mann-Whitney U test and Chi-square test respectively. When appropriate, box plots and cross tables will be used for descriptive statistics of continuous and categorical variables, respectively. OS will be estimated by the Kaplan-Meier method with corresponding two sided 95% Cl’s for survival proportions.

Primary and assisted technique efficacy rates (PTE, ATE) defined as the percentage of target lesions that have recurred after the initial local treatment and after additional local treatments regardless of the technique(s) used to treat the recurrence with a minimum follow-up period of 12 months after the last focal therapy;- Direct and indirect total cost of care for both treatment arms will be registered in the cost-effectiveness data collection matrix. Based on this matrix a cost–utility analysis, measured in terms of years of full health lived, using quality-adjusted life years will be prospectively calculated. Cost-effectiveness will be expressed as an ICER, the ratio of change in costs to the change in effects.

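### Pain has a pre-treatment score and repeated follow-up scores, but the only between-arm test named for it is an unadjusted rank test, with no pain score or visit fixed

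*Protocol article*

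**What the plan says.** All references are to the protocol article.

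- **Primary and secondary objectives** lists among the main secondary endpoints "length of hospital stay, assessment of pain and quality of life (QoL"). On measurement it says: "Pain analysis will be performed using visual analogue scale questionnaires (VAS) assessed prior to, directly after and every 3 months after local treatment".
- The same paragraph then turns to quality of life (QoL) and defines one value per patient: "The largest decrease in quality of life with respect to baseline will be calculated". It closes with: "The Wilcoxon rank sum test will be used to detect statistical differences between the two treatment arms". No corresponding summary is defined for pain.
- **Statistical methods** gives the general rule: "Significance of differences for continuous and categorical data will be analysed using the Mann-Whitney U test and Chi-square test respectively". On the threshold it says that P-"values below 0.05 will be considered significant".

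The Wilcoxon rank sum test and the Mann-Whitney U test are the same test. Whichever sentence is taken to govern pain, the named comparison is an unadjusted two-sample rank test at 0.05. Neither section says which VAS score, visit or summary enters it.

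**The concern.** A two-sample rank test takes one number per patient. If that number is a raw follow-up VAS, the test makes no use of the score taken before treatment, and none of the correlation between a patient's successive scores. The trial collects both, so the pain comparison would be less precise than the data allow.

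Because the score and visit are not fixed, the comparison also remains open to choice after the data are seen. This matters beyond the endpoint itself. The article's case for changing practice, if survival proves non-inferior, rests on lower morbidity and better quality of life, and patient-reported pain is part of that argument. It would be better supported by one defined estimate with an interval than by a p-value whose input is unspecified.

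**Working it through.** **Inputs from the article.** There are 309 patients per arm (Sample size calculation and statistical considerations) and a threshold of 0.05 (Statistical methods). The pain schedule gives five post-treatment scores in year 1: immediately after, and months 3, 6, 9 and 12.

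**Inputs assumed.** The article gives no correlation between baseline and follow-up VAS and no SD. I take r = 0.3 to 0.6. The formulas below are for mean differences in a linear model and only approximate what happens with a rank test on a bounded, skewed scale.

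**The plan's own figure.** There is no sample size or power statement for pain. The OS calculation reproduces: 359.3 events / 0.6 = 598.8, so 599. It has no bearing on this point.

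**1. Precision at one visit.** Variance with baseline adjustment, relative to the raw follow-up score, is 1 − r².
- r = 0.3: 1 − 0.09 = 0.91, a 9% reduction. The raw score needs 1/0.91 = 1.10 times the patients.
- r = 0.6: 1 − 0.36 = 0.64, a 36% reduction. The raw score needs 1/0.64 = 1.56 times the patients.

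The detectable difference at 80% power (two-sided 0.05, 309 per arm) is √(2/309) × (1.960 + 0.842) = 0.225 SD unadjusted. Adjusted, it is 0.225 × √0.91 = 0.215 SD at r = 0.3 and 0.225 × √0.64 = 0.180 SD at r = 0.6.

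**2. Rank test on change from baseline.** Variance of a change score, relative to the raw score, is 2(1 − r).
- r = 0.3: 1.40, worse than ignoring baseline.
- r = 0.6: 0.80, against 0.64 with adjustment.

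The ratio of change score to adjustment is 2(1 − r)/(1 − r²) = 2/(1 + r), which is 1.54 at r = 0.3 and 1.25 at r = 0.6. A change score therefore still needs about 54% to 25% more patients than baseline adjustment.

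**3. Using the repeated scores.** With equal correlation r between all scores, the baseline-adjusted mean of five visits has variance (1 + 4r)/5 − r² relative to one unadjusted visit.
- r = 0.3: 0.44 − 0.09 = 0.35.
- r = 0.6: 0.68 − 0.36 = 0.32.

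Most of this gain comes from averaging, and the quantity estimated is a 12-month mean, not a single-visit difference.

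**4. False positives, only if each year-1 score were tested at 0.05.**
- Independent tests: 1 − 0.95⁵ = 0.226.
- Simulated with equally correlated test statistics (400,000 runs): 0.208, 0.183 and 0.148 at correlations of 0.3, 0.5 and 0.7.

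The range is about 15% to 23%, against 5% for a single contrast.

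**The case against.** **The Mann-Whitney sentence is generic.** It does not mention pain and sits in a section that begins with clinicopathological and procedural variables. That is true, but the alternative is the Wilcoxon sentence closing the pain and QoL paragraph, which names the same test.

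**A reader might infer that pain will be tested visit by visit, so that false positives multiply.** The article does not say so. Carrying the inference to ten years of three-monthly scores (41 tests, 1 − 0.95⁴¹ = 0.88) goes further still. It assumes independent tests that no section proposes, and the Follow-up section moves the QoL questionnaires to six-monthly after year 1. Only the conditional year-1 figure is worth keeping.

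**A reader might also infer that a rank test cannot use the baseline.** It can, through a change or summary score, and the QoL rule does exactly that. This stands, but it does not remove the loss of precision. A change score is generally less efficient than baseline adjustment. The QoL rule is worded for quality of life, and the largest fall on a pain scale would measure relief, not harm.

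**The detail may be in a document not shown.** A journal article condenses the full protocol, and a statistical analysis plan may define the pain score and model. The mere absence of a named visit would not be a finding. The point here is that a better method exists than the one stated, using data the trial already collects.

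**A rank test on a skewed VAS is valid, and arm-level summaries will accompany it.** Both are correct. The issue is efficiency and a defined estimate of the arm difference, not validity.

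**Conclusion.** The point holds as a modest improvement to one secondary endpoint. On raw scores, the stated test leaves the baseline VAS and the repeated measurements unused. Under an assumed correlation of 0.3 to 0.6, baseline adjustment would reduce the variance by about 9% to 36%. If most patients start with little or no pain, the correlation could be lower and the gain small. These figures are linear-model approximations.

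The inflation of false positives to about 15% to 23% is conditional on separate tests of the five year-1 scores; it is not a feature of the plan as written. The primary OS conclusion is unaffected.

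**What to change.** State that VAS over the first 12 months will be analysed with one repeated-measures model containing treatment, visit, treatment by visit, and baseline VAS as covariate. Name one contrast in advance, for example the mean arm difference over those 12 months, and report it with its 95% CI. The team should decide beforehand whether the score taken immediately after the procedure belongs in that mean, since it may reflect a different kind of pain from the later scores. Report visit-specific differences as descriptive. Keep the rank test as a sensitivity analysis, because VAS is skewed.

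Limiting the contrast to 12 months also largely avoids comparing shrinking groups of survivors: the sample size section expects 60% deaths about 6.5 years after the last inclusion.

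The cost is analysis wording, with no new data. The downside is reliance on model assumptions, which the rank-based sensitivity analysis helps to check. If an existing analysis plan already specifies such a model, a cross-reference closes the point.
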